## Abstract

**Background:**

Childhood obesity is a public health issue negatively affecting children’s physical and psychosocial health. Mothers are children’s primary caregivers, thus key players in childhood obesity prevention. Studies have indicated that mothers underestimate their children’s weight. If mothers are unaware of their children’s weight problem, they are less likely to participate in activities preventing and treating excess weight. The “Healthy Change” intervention is designed to change maternal perception of child’s weight (MPCW) through peer-led group health education in childcare settings.

**Methods/Design:**

The “Healthy Change” is a multicenter two-arm randomized trial in four centers. Three centers are in Mexican States (Nuevo Leon, Tamaulipas, and Zacatecas). The fourth center is in San Antonio, Texas, USA. A total of 360 mother-child pairs (90 pairs per center) are to be randomly and evenly allocated to either the intervention or the control group. Intervention group will receive four-session group obesity prevention education. Control group will receive a four-session personal and food hygiene education. The education is delivered by trained peer-mother promotoras. Data will be collected using questionnaires and focus groups. The primary outcome is a change in proportion of mothers with accurate MPCW. Secondary outcomes include change in maternal feeding styles and practices, maternal self-efficacy and actions for managing child excessive weight gain.

McNemar’s Test will be used to test the primary outcome. The GLM Univariate procedure will be used to determine intervention effects on secondary outcomes. The models will include the secondary outcome measures as the dependent variables, treatment condition (intervention/control) as the fixed factor, and confounding factors (e.g., mother’s education, children’s gender and age) as covariates. Sub-analyses will be performed to compare intervention effects on primary and secondary outcomes between the samples from Mexico and Texas, USA. Qualitative data will be analyzed through analysis of inductive content. A combined coding model will be developed and used to code transcripts using the NVivo software.

**Discussion:**

Healthy Change intervention could help change MPCW, an initial step for obesity prevention among preschoolers. This study presents a first of its kind intervention available in Spanish and English targeting Mexican and Mexican-American mothers in Mexico and USA.

**Trial registration:**

ISRCTN12281648

## Background

Childhood obesity is a worldwide epidemic that disproportionally affects certain racial/ethnic groups [1]. Mexico is among the countries with the highest prevalence of childhood obesity [2, 3]. Obesity is more prevalent in Mexican-American children than their white counterparts in the United States of America (USA) [4]. Childhood obesity has been found to increase health risks, e.g. hyperlipidemia, hypertension and abnormal tolerance to glucose. In addition, it has been documented that overweight (OW) preschoolers were four times more likely to become obese (OB) adolescents than their normal weight counterparts [4]. Given the consequences of overweight and obesity on physical and psychosocial health, as well as the heavy economic burden on health care, Public Health interventions are urgently needed to fight this epidemic in both USA and Mexico [5].

Obesity is a multi-faced etiological disease with risk factors such as genetic predisposition [6], increased energy consumption, sedentary lifestyle, poor socio-economic status, as well sociocultural factors and false beliefs about childhood obesity [7, 8]. Unlike adults, children cannot choose the environment in which they live or the food they eat [9]. Mothers are influential in shaping life habits of young children, thus important agents for childhood obesity prevention [10, 11]. However, research has shown that mothers of young children, do not perceive overweight or obesity as a health threat. Instead, they prefer chubby children [12, 13]. In Mexico, a study on mothers and children residing in 5 northeastern states found that 68% of mothers of overweight children and 75% of mothers of obese children underestimated their preschoolers’ body weight [14]. In addition, Mexican and Hispanic mothers exert control and discipline that could lead to over consumption of foods and increased obesity risk [15, 16]. More problematic, when mothers were not aware of their children’s overweight status, they had a lower self-efficacy to manage behaviors related to their child’s weight in comparison to mothers of normal weight children [17, 18]. Such research findings highlight the need for correcting mothers’ misperception of their children’s overweight status as the first step for obesity [8, 19, 20].

Childhood obesity prevention programs should incorporate strategies targeting mothers’ misperception of their children’s weight status. A study conducted in Iran documented the impact of an educational intervention on maternal perception of school children’s weight. The study showed a significant increase in the capacity of mothers to recognize their children’s obese weight status [21]. Interventions to prevent and treat OB in preschool Mexicans are scarce and have been directed to diet and exercise, showing little effect or none [22]. Also in these interventions, maternal perception of children’s weight has not been evaluated (MPCW) prior to incorporate participants in the intervention programs. As such, the “Healthy Change” intervention is designed to change maternal misperception of her child’s weight (MPCW) through peer-led parental education in childcare settings.

## Methods

### Aims

This pilot study aims to develop and test the effects of the “Healthy Change” intervention on changing maternal perception of preschoolers’ weight status among Mexican mothers in México, and Hispanic mothers in San Antonio, Texas. Specific objectives are 1) To test the feasibility of “Healthy Change” intervention when implemented in a childcare setting; 2) To assess the effect of “Healthy Change” intervention on changing maternal perception of their preschoolers’ weight status; and 3) To assess the effect of the “Healthy Change” intervention on changing parenting style, maternal attitude, self-efficacy and practice toward raising healthy weight children.

### Trial design

The “Healthy Change” study is a multicenter two-arm randomized trial with four research sites, three in Mexico: a) Nuevo León, b) Tamaulipas, and c) Zacatecas, and one in San Antonio, Texas, USA. At each site, two childcare centers are randomly assigned to either the intervention or the attention control group. A total of 360 pairs of preschoolers and their mothers, i.e., 90 pairs per site, are recruited for the trial. Intervention participants will receive a four-weekly group education focusing on maternal perception of children’s bodyweight that facilitate healthy behavioral changes for the family. Control participants will receive a four-session group education on food hygiene and first aids as attention control. The outcomes include change in the proportion of mothers who accurately estimate their children’s weight categories, change in feeding style, maternal self-efficacy and actions taken in managing the child’s excessive weight gain. Data are to be collected at baseline and the end of the four-week group education from both groups. The study began on 08–29-2015, and will end on 11–20-2018.

### Study setting

The study will be conducted in childcare settings, i.e., kindergarten classes in Mexico and Head Start Centers in Texas, USA.

### Sample size and statistical power

The primary outcome of this intervention will be the proportion of mothers who adequately estimate their child’s weight status. Assuming the intra-class correlation coefficient (ICC) of 0.03, to detect a change of mother’s accurate estimation of children’s weight status from 50 to 70% with 80% power, 37 mother-child pairs would be required per research center per arm [23]. Accounting for a 15% attrition rate, each research site will enroll 45 pairs of mothers and children for the intervention and another 45 pairs for the control group. The total sample size for this four-center trial will be 360 pairs of mothers and children.

### Childcare center recruitment and randomization

Each research site will recruit a total of 90 pairs of preschoolers and their mothers with 45 pairs in the intervention and 45 pairs in the control group. Each research site initially recruits two childcare institutions with similar size and demographic profiles to participate in the study. The administrators of these centers are informed of the possibility of being assigned to either the intervention or the control group. Prior to participant recruitment, the two or three childcare institutions at each research center are randomly assigned to one of the two treatment groups using a random number table. In the event that an insufficient sample is recruited from the participating centers, a third center will be added to ensure adequate sample in the designated group.

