### Participant recruitment

Participants will be recruited through meetings, flyers, and take-home letters. Interested parents will be screened for study eligibility and informed consent will be obtained prior to data collection.

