Attention control is considered a valid control condition when conducting trials of social-behavioral interventions such as Healthy Change. We developed an attention control curriculum with a similar dose of group education entitled: *“Hygiene and Health Promotion”*. The four weekly group sessions cover the following topics: 1) The mother as her child’s hygiene promoter; 2) Hygiene and food safety at home; 3) Best ways to store food in your kitchen; and 4) Accident prevention at home and surrounding areas.

Each session for both groups will last about 90 min and will be held in a room within the participants’ own childcare institution. Both the Healthy Change and Hygiene and Health Promotion curriculum are available in two languages, Spanish and English. In Mexico, the content is delivered in Spanish. In the USA, mothers select the language of their preference for group education.

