#### Healthy change intervention effect

The quantitative data will be analyzed in Statistical Package for the Social Sciences (SPSS) version 23. WHO Anthro (version 3.2.2, January 2011) and macros will be used to calculate children’s age- and gender- specific BMI percentile and children will be classified by the World Health Organization | BMI-for-age chart: malnutrition (percentile < 3), low weight (≥3 and < 15), normal weight (≥15 and < 85), OW (≥85 but < 97), and OB (≥97) [31]. The rate at which mothers accurately classify their children’s weight status will be calculated in two ways, i.e., by words or by images. Accurate MPCW by words will be defined as show in Table 2.

**Table 2 Tab2:** Accurate MPCW by words

Children’s actual weight status by BMI percentile	MPCW by words
Malnutrition (< 3 percentile) Low weight (≥ 3 and < 15 percentile)	“underweight” or “a little underweight”
Normal weight (≥ 15 and < 85 percentile),	“Normal weight”
Overweight (≥ 85 but < 97 percentile)	“A little overweight”
Obese (≥ 97)	“Overweight”

With regard to the MPCW by image test, an accurate perception is defined when mothers of underweight and normal weight children select an image smaller than the average image or when mothers of children with OW-OB select the average or a larger image.

McNemar’s Test will be used to test the primary outcome measure, i.e., intervention effect on change in proportion of mother’s accurate recognition of their preschooler’s weight status. The GLM Univariate procedure will be used to determine intervention effects on secondary outcomes e.g., scores of mother’s self-efficacy, feeding practices and children’s BMI percentiles and fat%. The models will include the secondary outcome measures as the dependent variables, treatment condition (intervention versus control) as the fixed factor, and confounding factors (e.g., mother’s education level, children’s gender and age) as covariates. Sub-analyses will be performed to compare intervention effects on both primary and secondary outcomes between the samples from Mexico and Texas, USA.

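### Centres are allocated before mothers are invited, consented and measured, and no safeguard is described, so who enrols may differ by arm

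*Protocol article*

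**What the plan says.** The protocol article randomises childcare centres within each of four sites. Under Trial design: "At each site, two childcare centers are randomly assigned to either the intervention or the attention control group". Under Childcare center recruitment and randomization it gives the timing: "Prior to participant recruitment, the two or three childcare institutions at each research center are randomly assigned to one of the two treatment groups". The same section provides that, if too few mothers are recruited, "a third center will be added to ensure adequate sample in the designated group".

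Participant recruitment comes after that draw: "Participants will be recruited through meetings, flyers, and take-home letters". Screening happens at this stage, and "informed consent will be obtained prior to data collection". Consent and baseline measurement therefore both follow allocation.

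The Intervention section gives the two arms plainly different topics (the child's weight and feeding, against hygiene, food safety and accident prevention) and says each session "will be held in a room within the participants’ own childcare institution".

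In the section on intervention effect, the primary outcome (change in the proportion of mothers who classify their child's weight accurately) is tested with McNemar's test, with no covariates. The models for secondary outcomes include "confounding factors (e.g., mother’s education level, children’s gender and age) as covariates".

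**The concern.** Randomising centres protects the comparison of centres. It does not protect the choice of mothers within centres if that choice is made after the arm is settled. Here enrolment is voluntary, and the two courses would interest different mothers. Whether a mother joins a course on child weight may depend on how she already sees her child's weight, on the child's actual weight status (which determines the correct answer in Table 2), or on how ready she is to change. All three bear on the primary outcome.

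If enrolment differs by arm in these respects, an arm difference at follow-up mixes the effect of the education with the effect of who came. With two centres per site and four sites there are 8 centres, 4 per arm before any third centre is added. That number gives little scope for such differences to average out, and selection that follows the arm would not average out with more centres either.

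**Working it through.** **Order of events, section by section**

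1. Two centres of similar size and demographic profile are recruited at each site, and administrators are told either assignment is possible (Childcare center recruitment and randomization).
2. The centres are allocated before any mother is recruited (same section).
3. Mothers are invited, screened and consented (Participant recruitment).
4. Baseline data are collected.
5. If numbers fall short, a third centre is added for the arm that needs it. That section can also be read as allocating a third centre in advance. On either reading, its arm is settled before its mothers are invited.

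Step 2 comes before steps 3 and 4. Step 5 requires staff to know which arm is short. So recruiters can know the arm. Mothers can learn it because each centre runs one curriculum on site. The article mentions no masked recruiter, no invitation or consent form neutral between arms, and no listing of eligible mothers before the draw.

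**The plan's own figures**

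The article gives no figure for recruitment bias. Its sample size is used below only to set the precision of an illustration.

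- Inputs (Sample size and statistical power): 50% to 70%, ICC 0.03, 37 pairs per centre per arm, 80% power. Alpha is not stated.
- Design effect: 1 + (37 − 1) × 0.03 = 2.08.
- The figure of 37 is reproduced with a one-sided 5% test and unpooled variance: 71.1 per arm unclustered, and 71.1 × 2.08 / 4 = 36.97.
- Effective number per arm: 4 × 37 / 2.08 = 71.2.

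This neither supports nor weakens the point, which concerns the order of recruitment and allocation.

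**Illustration (the enrolment ratios are assumptions)**

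Suppose 50% of mothers are accurate in both populations, the education has no effect, and enrolment in control centres is unrelated to accuracy. Let accurate mothers be r times as likely as others to enrol in intervention centres. The proportion accurate among intervention enrollees is then r / (1 + r), and the spurious arm difference is r / (1 + r) − 0.5. The last column is the rejection rate of a two-sided 5% comparison of two proportions at follow-up, with 71.2 effective mothers per arm.

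| r | Proportion accurate | Spurious difference | Share of 20-point target | Type I error |
|---|---|---|---|---|
| 1.1 | 52.4% | 2.4 points | 12% | 5.9% |
| 1.25 | 55.6% | 5.6 points | 28% | 10.2% |
| 1.5 | 60.0% | 10.0 points | 50% | 22.6% |
| 2 | 66.7% | 16.7 points | 83% | 53.4% |

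Ratios of 1/1.25 and 1/1.5 give −5.6 and −10.0 points: the same size, in the opposite direction.

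**What a change measure does to this**

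Take r = 1.5 with no effect. Intervention mothers are 60% accurate before and after, and control mothers 50% before and after. The post-only difference is 60 − 50 = 10 points. The difference in change is (60 − 60) − (50 − 50) = 0. A pure baseline gap therefore drops out. If one arm instead enrols more mothers who are ready to revise their view, the changes themselves differ and nothing cancels. The article gives no figure from which to size that part.

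**The case against.** Only the order of events is documented. The article names the recruitment channels but not what the materials disclose, who recruits, or how the consent form is worded. A condensed article may leave masking of recruiters to the full protocol. A reader might infer that mothers and recruiters do know the arm; the text supports only that recruiters can know it and mothers can learn it. This objection stands and limits the wording, but masking described elsewhere would not alter the stated order.

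The primary outcome is a change, tested on paired data. A reader might take the 28% to 50% in the table as the bias in the primary result. That does not follow: those figures belong to an unadjusted post-only comparison, which the plan does not state for its primary outcome. McNemar's test works within a group, so the concern bites on any between-arm reading of it and on the secondary models, which compare arms directly. The covariates named belong to those secondary models only, and the examples given include neither baseline perception nor motivation.

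A reader might also assume that weight-conscious mothers favour the intervention arm, inflating the effect. The opposite is equally plausible: mothers confident in their own judgement may see less need for such a course.

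Some features help. The initial centres are similar in size and profile, the control course has a similar dose, and every mother receives the same payment. These even out burden and incentive, but not interest in the topic.

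Finally, the abstract's statement that pairs "are to be randomly and evenly allocated to either the intervention or the control group" concerns the unit of allocation. It says nothing about timing and is not evidence here.

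**Conclusion.** The point holds as a design weakness. Followed as written, the plan allows enrolment to be shaped by a known arm, for the initial centres and more clearly for any third centre. This rests on the stated order of events and on the absence of any described safeguard. It does not rest on proof that mothers knew their arm.

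The size and direction of the bias cannot be derived from the document. Under the assumed enrolment ratios of 1.25 to 1.5, a post-only comparison would be off by 5.6 to 10.0 points in either direction. A comparison of change would remove the part due to a baseline gap in accuracy and leave the part due to readiness to change, which remains unquantified. The point merits a change to the plan, but it does not show that the trial's result will be biased.

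**What to change.** At each site, recruit both centres and any reserve third centre up front. Use one invitation and one consent form that describe both curricula. Complete the baseline questionnaires and measurements in all of them, and only then draw and release the allocation. Any shortfall in numbers then shows before the draw, so a third centre can be brought in without its arm being known.

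Where a site is already randomised, or a centre is added later to a known arm, report the numbers eligible and enrolled and the baseline accuracy by arm, and adjust the between-arm analysis for baseline accuracy. Baseline perception is already collected, so this needs no new measurement. It cannot repair selection on readiness to change.

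The cost is a delay between baseline and session 1. Curriculum-specific promotora training (the 6 hours of training include session content), the certification exam, and any remediation and retake would have to fit into it. Training on the overall study and on communication skills could come before the draw. Some mothers may withdraw once the arm is released. That loss would count against the 15% attrition allowance, but it would be visible by arm and could be described from baseline data, which is not possible for mothers who never enrol.

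### The rule for adding a third childcare centre conflicts with randomising all centres before recruitment, and appears to set that centre's arm by recruitment need

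*Protocol article*

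**What the plan says.** Under Trial design, the protocol article describes the base design: "At each site, two childcare centers are randomly assigned to either the intervention or the attention control group".

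The section Childcare center recruitment and randomization gives the detail:

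- Target per site: "90 pairs of preschoolers and their mothers with 45 pairs in the intervention and 45 pairs in the control group".
- Starting point: "Each research site initially recruits two childcare institutions with similar size and demographic profiles to participate in the study". Administrators are told that either assignment is possible.
- Draw: "Prior to participant recruitment, the two or three childcare institutions at each research center are randomly assigned to one of the two treatment groups", by random number table.
- Contingency, in the sentence directly after the draw: its trigger is a shortfall in the mothers recruited from the centres already taking part, and the response is that "a third center will be added to ensure adequate sample in the designated group".

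No random step is described for the added centre, and the article does not say how its group is designated.

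**The concern.** The last two statements are consecutive and do not fit together. One places every centre, including a third, in a draw held before recruitment. The other brings the third centre in because recruitment has already fallen short, and sends it to a group that needs mothers.

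If the contingency is used as written, one arm at that site would contain a centre whose arm was not drawn. Its mothers would be recruited later, and it would have no counterpart in the other arm. The two starting centres are chosen to be alike in size and demographics, and both accept that they may get either arm. Neither safeguard is stated for the added centre. Sessions are held in the mothers' own childcare institution and are led by promotoras recruited from participating centres, so an added centre may also bring its own sessions and promotora to one arm only. With one centre per arm at each site, few randomised units are available to dilute this.

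**Working it through.** **1. The recruitment target.** The contingency refers to an insufficient sample without giving a threshold; the natural yardstick is the target of 45 pairs per arm per site. Sample size and statistical power states "37 mother-child pairs would be required per research center per arm" and 15% attrition.

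- 37 / (1 − 0.15) = 43.5, rounded up to 44, against 45 stated: close agreement.
- 45 × 2 arms × 4 sites = 360: exact agreement.

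No sample-size figure changes because of this point. The question is one of allocation.

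**2. Timing.** The draw comes before participant recruitment. The trigger is that too few participants have been recruited, which can be known only after recruitment starts. Sites begin with two centres, so a third added on this trigger was not available at that draw.

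**3. Allocation.** Each arm at the site already has one centre. If the third were assigned by a fair 1:1 draw, it would reach the arm short of mothers with probability 0.5. To ensure the sample in that arm, it must be placed there with probability 1, which is not random assignment.

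**4. What a bias would depend on.** The primary outcome is a change in the proportion of mothers who classify their child's weight accurately, measured at baseline and after the sessions. Let *w* be the share of an arm's mothers who come from the added centre, and *d* the difference between that centre's change in accuracy and the change among the arm's other mothers. The arm's mean change then moves by

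shift = *w* × *d*.

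A centre whose mothers are more or less accurate by the same amount at both visits has *d* = 0 and leaves the arm's change unaltered.

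The document gives neither *w* nor *d*. Purely as an illustration, assume that the centre supplies 20 of the 45 mothers and that *d* is 10 to 20 points:

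- That site's arm: 20/45 × 10 to 20 points = 4.4 to 8.9 points.
- The whole arm, if only one site adds a centre (45 × 4 = 180 mothers): 20/180 × 10 to 20 points = 1.1 to 2.2 points.

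The planned effect is 20 points (50% to 70%). With *d* = 0 both shifts are zero.

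**5. A plausibility check on level differences.** Under the article's ICC of 0.03 and a proportion of 50%, the between-centre SD of the level is √(0.03 × 0.50 × 0.50) = 8.7 points. The SD of the difference between two exchangeable centres is √2 × 8.7 = 12.2 points. A 20-point gap at one site is then 20/12.2 = 1.6 SD. An average gap of 20 points in the same direction at all four sites has SD 12.2/√4 = 6.1 points, and so is 20/6.1 = 3.3 SD. Chance differences between centres could give a sizeable gap at one site, but hardly the same large gap at all four. This check concerns level only; the article gives no ICC for change.

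**The case against.** The strongest defence is that the sentence on the draw expressly covers a third centre. The designated group could then mean the arm drawn for a reserve centre in advance, or drawn later but before that centre's own mothers are approached. The article never says outright that the group is the one short of mothers. This is why the point is put as an apparent non-random allocation and not as a certain one. The reading is strained, though: sites start with two centres, the third is added on a shortfall, and a draw cannot ensure the sample in a chosen group.

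Three stronger inferences are tempting, and the defence is right to resist them:

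- *The Trial design section contradicts the recruitment section.* It does not. It summarises the base design of two centres per site and omits a contingency. The conflict lies between the two consecutive sentences in the recruitment section.
- *The added centre's allocation is related to the outcome.* Recruitment could differ by arm, because centres are assigned before mothers are recruited, and that would make the placement recruitment-related. Nothing in the article links a shortfall to mothers' accuracy.
- *A bias of several points can be read off.* It cannot. The inputs are assumed, and a difference in level alone does not bias a change outcome.

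It is also fair to say that the contingency may never be used, that the study calls itself a pilot, and that centre and arm are already confounded within each site when each arm has one centre. These points limit the weight of the concern. They do not resolve the conflict, because the article states a rule and has not merely left out a detail.

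**Conclusion.** The point holds as a conflict between two adjacent sentences. It also holds as an allocation rule that, taken as written, would place a later-recruited, non-randomised cluster in one arm of a site. The conclusion assumes that the designated group is the one short of mothers, which is the most natural reading of a rule meant to secure the sample in that group.

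The size of any bias is unknown. It is zero if the contingency is never used, or if the added centre's change matches that of the arm's other mothers. Otherwise it is the product of the centre's share and its difference in change, neither of which the article supplies. The illustrative shifts show how that product scales and are not estimates. A reader should not conclude that the trial's allocation is outcome-related, or that the overall comparison is off by a stated number of points. The matter should be corrected because the rule weakens the randomisation whenever it is used and the correction is cheap.

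**What to change.** Reword the two sentences in Childcare center recruitment and randomization so that reserve centres are identified before randomisation and included in the same random draw. Draw one reserve for each arm, so that a reserve activated in a short arm was itself randomised to that arm. State what counts as a shortfall.

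If a centre is added, or has already been added, without a draw, report the site, the arm and the number of mothers. Give a sensitivity analysis of the primary outcome excluding those mothers. The analysis is suggested for that case; its absence from a condensed article is not itself a fault.

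The cost is a change of wording, earlier contact with reserve centres (two per site, so 2 × 4 = 8 if every site holds one for each arm), and at most one extra analysis. The sample size does not change.
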